### 4.4 Sample size calculation

Inname van 10 mg luteïne uit een voedingssupplement laat een toename zien in de hoeveelheid macula pigment van 5% per maand [57]. Inname van 20 mg luteïne laat een vergelijkbare toename zien [58]. De hoeveelheid luteïne in één ei per dag ligt maximaal op 1 mg. Echter de beschikbaarheid van luteïne in eieren is veel groter dan in voedingssupplementen. We verwachten daarom op zijn minst een toename van 3% per 4 weken, hetgeen resulteert in 9% toename in 3 maanden.

De hoeveelheid macula pigment zal worden bepaald met de Macula Pigment Reflectometer, die een meetfout heeft van 7% [21]. We willen drie groepen met elkaar vergelijken. Om een significant verschil in macula pigment dichtheid van 9% aan te kunnen tonen zijn dan 18 proefpersonen per groep bij  $\alpha=0.5$  (Bonferroni correctie 0.017) en  $\beta=0.1$  nodig [59].

Uitgaande van 10% uitval, komen we op 20 proefpersonen per groep.

**Opmerking [TB1]:** Intake of 10 mg lutein from supplements induces a 5% monthly increase in MPOD [57]. Intake of 20 mg induces a similar increase [58]. Although the amount of lutein per egg is much less, the bioavailability is higher. We therefore anticipated a 3% monthly increase in MPOD, resulting in a 9% MPOD increase over the study period. The repeatability of the QuantifEYE is 11.7%. With  $\alpha=0.05$  and  $\beta=0.1$  this yielded 18 subjects per group [59]. Taking into account a 10% dropout we included 20 subjects per group.

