## 2. OBJECTIVES

Primary Objective: Assessing macular pigments' spatial distribution and the changes after consumption of modified eggs compared to normal eggs.

Secondary Objective(s): Assessing changes in retinal morphology, visual acuity and contrast sensitivity. We will also evaluate lipoprotein metabolism in relation to daily egg consumption.

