### 3. STUDY DESIGN

This will be a randomized placebo-controlled trial. The total study time will be two years of which 3 months actual trial and follow up time. Every individual will have 3 measuring point at set interval. At every measuring point (days 1, 45 and 90) these subjects will undergo 6 different non-invasive measuring techniques. These are the mean visual acuity test using the Early Treatment Diabetic Retinopathy Study (ETDRS)-chart, contrast sensitivity using the Pelli-Robson chart, Scanning Laser Ophthalmoscope (SLO), Optical Coherence Tomography (OCT) and Heterochromatic Flicker Photometry (HFP) and the Reflectometer. A questionnaire will be taken at the beginning of the trial. The invasive part of the study involves blood sampling at all three times, measuring the serum concentration of lutein, zeaxanthin, omega-3 and lipoprotein using the HPLC analysis.

At the beginning and twice more during the trial period, test subject will keep a nutrition diary for one day.

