## 6. METHODS

### 6.1 Study parameters/endpoints

#### 6.1.1 Main study parameter/endpoint

Macular pigment optical density: the amount of measurable macular pigment in the macula region.

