#### **Contrast sensitivity**

Subjects will be seated with both chin and head supported by the chin and head rest looking straight ahead to a computer monitor at 2.25 meter away. One eye, the one not being tested, is blindfolded. The researcher will then instruct the subject to look at the monitor onto which a circle is displayed with clearly visible vertical stripes in black and white (and all the greyscale tones in between). These will alternate in a sinusal rhythm. The researcher can then change the contrast manually. Subjects are then instructed to say “yes” and “no” as to whether or not they see the stripes. In this manner the researcher will get ever closer to the threshold value for contrast sensitivity of the test subject. Once this value is reached the computer automatically changed to the next spatial frequency (subjects will be test on a total of 6 frequencies). Each time the researcher will adapt the contrast until the threshold is reached. This will continue for up to 10 minutes, depending on visual acuity and contrast sensitivity of subjects.

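### Section 4.4 sizes the primary endpoint on two different instruments with the same 18 per group, and neither the endpoint definition nor the analysis section says which one is primary

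*Protocol*

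**What the plan says.** Protocol 4.4 holds two accounts of the same calculation.

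- **Dutch body text.** Macular pigment "zal worden bepaald met de Macula Pigment Reflectometer" (will be determined with that device), "die een meetfout heeft van 7% [21"] (a 7% measurement error). Three groups are to be compared, with a Bonferroni alpha of 0.017 and beta 0.1. The overall alpha is printed as 0.5; since 0.05/3 = 0.0167, it is evidently meant as 0.05.
- **English comment TB1.** "The repeatability of the QuantifEYE is 11.7"%, with alpha 0.05, no Bonferroni step, and beta 0.1.

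Both assume a 9% rise in pigment, both state 18 per group, and both go to 20 for 10% dropout.

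The QuantifEYE does not appear in the visit table, the design section or the procedures. Section 6.1.1 defines the endpoint as "Macular pigment optical density: the amount of measurable macular pigment in the macula region", without instrument or time point. Section 8 models change in pigment density over time and also names no instrument. The SLO, HFP and Reflectometer are all scheduled on Days 1, 45 and 90.

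The primary objective in Section 2 is "Assessing macular pigments' spatial distribution and the changes after consumption of modified eggs compared to normal eggs". Objective 1 in the Summary is simply change in macular pigmentation.

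Contrast sensitivity, a secondary parameter, is also described in two ways. Section 3 has "contrast sensitivity using the Pelli-Robson chart", as does the Summary. Section 6.3 describes striped gratings on a computer monitor at six spatial frequencies, where "The researcher can then change the contrast manually".

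**The concern.** A sample size belongs to one measurement with one variability. Here the same 18 per group is attributed to two devices, two error figures and two significance levels. At most one of these can describe the primary test, and the sections that should settle the matter (6.1.1 and 8) are silent.

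Two things are at stake. The first is power: if the primary result comes from the device in TB1, the stated 90% may not apply to it. The second is the type I error: while two devices each have a claim to be primary, the document does not by itself prevent a choice between them once results are known. Section 6.2 states that there is no blinding, so a fixed primary measurement matters all the more.

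The Section 2 objective adds a further mismatch. It speaks of spatial distribution, whereas the endpoint and both sizings concern a percentage change in an amount of pigment. No effect size or SD is given for spatial distribution, so no sample size can be derived for it.

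**Working it through.** **Inputs (all Protocol 4.4).** Difference 9%; power 0.90; Reflectometer error 7% with alpha 0.017; QuantifEYE repeatability 11.7% with alpha 0.05; 18 per group; 10% dropout. Sidedness is not stated; two-sided is assumed. The protocol does not say what either percentage represents, so each is first taken as the SD of the quantity compared.

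**Formulas.**
- Two groups, normal approximation: n per group = 2 (z₁₋α/₂ + z₁₋β)² (SD/9)². The t-test versions use the noncentral t distribution.
- Within group, before-after: n = (z₁₋α/₂ + z₁₋β)² (SD/9)².

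**Step 1. Reflectometer basis.** 2 × (2.387 + 1.282)² × (7/9)² = 16.3, so 17. The two-sample t-test gives 18, with power 0.904 at 18. The stated figure is reproduced. Dropout: 18/0.9 = 20, also reproduced.

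**Step 2. QuantifEYE basis, two groups.** 2 × (1.960 + 1.282)² × (11.7/9)² = 35.5, so 36. The t-test gives 37, with power 0.61 at 18. The stated 18 is not reproduced.

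**Step 3. Where TB1's 18 could come from.** The within-group formula gives (1.960 + 1.282)² × (11.7/9)² = 17.8, so 18 (the paired t-test gives 20). That is a before-after test in a single group. The Section 2 objective is a comparison of modified with normal eggs.

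**Step 4. Other meanings of 11.7%, two-group t-test, alpha 0.05.**

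| Reading of 11.7% | SD used | n per group | Power at 18 |
|---|---|---|---|
| SD of the compared quantity | 11.7 | 37 | 61% |
| 1.96 × SD of differences | 11.7/1.96 = 5.97 | 11 | 99% |
| Single-measurement SD | 11.7 × √2 = 16.5 | 73 | 35% |

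None of the three gives 18. The Reflectometer figure is open to the same question: if 7% is a single-measurement SD, the change SD is 7 × √2 = 9.9, and alpha 0.017 requires 35 per group.

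**Step 5. Cost of leaving two candidates open.** This is the chance that at least one of two correlated tests, each at two-sided 0.05, is significant when there is no effect. It is 9.5% at correlation 0.3, 9.1% at 0.5 and 7.8% at 0.8. The correlations are assumed; the protocol gives none.

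**The case against.** The best reply is that the body text does commit to one device. The Dutch sentence names the Reflectometer, its sizing reproduces, and it therefore defines a coherent test. TB1 is a margin comment, and the other comments (TB2 to TB4) are translations. On this view TB1 is a faulty translation and the Dutch text governs. The first part stands: it would be wrong to say that the stated alpha and power belong to no definable test. But nothing in the protocol says which text governs, and TB1 is the only English account of the calculation.

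Four stronger readings are tempting, and the documents do not support them.

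- **Three competing primary instruments.** Three candidate devices are scheduled, but only the Reflectometer procedure says that its output is macular pigment. HFP is linked to pigment through the title of the reference cited for it. The SLO text says only that pictures of the macula are taken in different colours. Nor does the protocol say that the QuantifEYE is the HFP device. A false-positive rate built on three instruments (10 to 14% at 0.05) therefore rests partly on inference.
- **Power falling from 90% to 43%.** The 43% pairs TB1's 11.7% with the Dutch text's alpha of 0.017, a combination stated nowhere. At TB1's own alpha the figure is 61%, and under one reading of repeatability power is above 90%. Even the direction depends on what 11.7% means.
- **A choice made after seeing the data.** TB1 is written in the past tense, which may suggest a late addition. That is no evidence of selection, and an analysis plan that is not shown here may fix the instrument.
- **A wholly open time point.** Section 6.1.1 gives none, but 4.4 refers to an effect over three months, which points to Day 90, and Section 8 puts time in one repeated-measures model.

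**Conclusion.** The point holds as a contradiction within 4.4 that the rest of the protocol does not resolve. The Reflectometer basis supports 18 per group at 90% power if 7% is the SD of the compared quantity. The QuantifEYE basis does not give 18 for a two-group comparison under any of the three readings tried: the requirement is about 11, 37 or 73 per group, with 99%, 61% or 35% power at 18. It matches only a within-group before-after calculation.

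If either of the two named devices could be reported as primary at 0.05, the error per contrast is about 8 to 10% instead of 5%. HFP and SLO readouts might add to this, by an amount the text does not allow one to state.

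These results assume two-sided tests, the readings of the error figures shown above, and correlations of 0.3 to 0.8. The mismatch between objective and endpoint is real but easily mended, since the Summary already words the objective as change in pigmentation. The contrast-sensitivity conflict is a separate inconsistency in a secondary parameter and has no bearing on the primary alpha or power.

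**What to change.** 1. In 6.1.1, name one instrument and define the primary endpoint as change in macular pigment optical density from Day 1 to Day 90. The Reflectometer is the natural candidate, because it is the device of the main text and its stated sizing reproduces.
2. In 4.4, state what the chosen device's error figure represents (SD of change, single-measurement SD, or a repeatability limit). Make the Dutch text and TB1 agree on instrument, SD and alpha, and correct the printed alpha of 0.5.
3. List any other pigment readouts and all Day 45 values as secondary, and name the primary instrument in Section 8.
4. Reword the Section 2 objective to match the density endpoint, or give spatial distribution its own secondary endpoint.
5. Separately, reconcile the contrast-sensitivity method across the Summary, Section 3 and Section 6.3.

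If the Reflectometer is kept and 7% is confirmed as the SD of the compared quantity, the cost is wording only, since its measurements are already scheduled. If another instrument is kept, or the error figure means something else, the power at 18 per group must be restated and the group size may have to change. Rewording the primary objective narrows a scientific aim, so the investigators should agree to it explicitly.

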### Objective:

1. Assess any change in macular pigmentation due to lutein and zeaxanthin enriched egg consumption. Our hypothesis is that eggs are very effective at increasing macular pigment optical density by increasing the amount of lutein and zeaxanthin in the *macula lutea*.
2. Assessing changes in retinal morphology, visual acuity and contrast sensitivity. We will also analyze lipid profile in its relation to daily egg consumption.

This study uses some of measuring techniques mentioned in protocol id MEC 06-1-052 where tropicamide is also used and also measures macular pigment optical density.

**Study design:** Randomized placebo controlled interventional trial, where subjects divided into 5 groups, will be consuming either no eggs, normal eggs (lutein:  $0.168 \pm 0.08$ , zeaxanthin  $0.085 \pm 0.0017$ ), eggs enriched with lutein (lutein:  $0.921 \pm 0.106$ , zeaxanthin:  $0.137 \pm 0.014$ ), eggs enriched with zeaxanthin (lutein:  $0.174 \pm 0.014$ , zeaxanthin:  $0.487 \pm 0.031$ ), or egg product made from the lutein enriched eggs. The omega-3 concentration is the same for all eggs and is  $200 \pm 10$ mg. Subjects will pick up their test product (if applicable) at every control session and twice between every control session they will have to come to the Human Biology distribution department to receive additional products. The control group

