#### Influence of modified eggs on macular pigment

will be asked to not consume any addition eggs to what they normally do, and everyone will be asked not to make any substantial change to their normal diet.

**Study population:** Healthy human volunteers, 18 years and older.

**Intervention (if applicable):** Each individual will consume one egg or egg product daily for 90 days. The trial group will receive the modified eggs or egg product while the control group will receive conventional egg.

| In egg (mg/egg) | Lutein
Mg per egg yolk |          | Zeaxanthine
Mg per egg yolk |          |
|-----------------|---------------------------|----------|--------------------------------|----------|
|                 | mean                      | St dev   | mean                           | St dev   |
| Control         | 0,16778                   | 0,008655 | 0,08504                        | 0,001692 |
| Lutein          | 0,921422                  | 0,105767 | 0,137318                       | 0,013953 |
| Zeaxanthine     | 0,1743                    | 0,014454 | 0,487303                       | 0,031019 |

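### The primary comparisons, their reference arm and their significance level are stated inconsistently, so control of the family-wise error cannot be established from the protocol

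*Protocol*

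**What the plan says.** **Number of arms.** The Summary (Study design) describes "subjects divided into 5 groups": no eggs, normal eggs, lutein eggs, zeaxanthin eggs, and a product made from the lutein eggs. Section 4.1 includes 100 subjects, which is 5 × 20.

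**Number of groups in the error control.** Section 4.4, in Dutch, says "We willen drie groepen met elkaar vergelijken", that is, three groups are to be compared with each other. They are not named.

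**Level.** The Dutch text prints alpha as 0.5 with "Bonferroni correctie 0.017". English comment TB1 in the same section gives alpha 0.05 and is silent on correction. It also changes the device and its error, from the Reflectometer at 7% to the QuantifEYE at 11.7%, yet reaches the same 18 per group.

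**Reference arm.** In the Summary (Study design) the control group "will be asked to not consume any addition eggs to what they normally do". Under Intervention, the modified products go to the trial group "while the control group will receive conventional egg". The egg-content tables also label the conventional egg as control. Section 2 sets the primary comparison as modified against normal eggs.

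**Analysis.** Section 8 plans a repeated-measures general linear model for macular pigment, with time, age and iris colour. It names no arm, contrast or level.

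**The concern.** A Bonferroni level has meaning only for a stated list of tests. Here the list is given by a count, three, that does not match the five arms, and the count carries no names. Three groups compared pairwise give three tests. Three modified products against normal eggs also give three tests, but involve four groups. Either could lie behind 0.017, and on the first reading two randomised arms fall outside the error control.

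The choice of reference arm changes the question. A comparison with the no-egg arm mixes the effect of eating an egg daily with the effect of enrichment. A comparison with normal eggs is the one that Section 2 asks for.

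An analyst could follow one sentence or another and arrive at different families and different levels. Section 6.2 says that there is no blinding, so such a choice could be made with results by arm in view.

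**Working it through.** **Inputs.** Difference 9% ("resulting in a 9% MPOD increase over the study period"); SD 7% (Dutch text) or 11.7% (TB1); beta 0.1; alpha 0.017 or 0.05; 18 per group, 20 after 10% dropout (all Section 4.4). Two assumptions are mine: tests are two-sided, and the quoted measurement error or repeatability acts as the SD of the quantity compared.

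**1. The plan's own figure, Dutch version.** 0.05/3 = 0.0167, which rounds to 0.017.

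n = 2 × [SD × (z₁₋α/₂ + z₁₋β)/difference]² = 2 × [7 × (2.394 + 1.282)/9]² = 16.4, so 17 per group. The exact two-sample t-test gives power 0.882 with 17 and 0.903 with 18, so it needs 18. Then 18/0.9 = 20. The stated figure is reproduced. With alpha 0.5 as printed, the same formula gives only 5 per group, so 0.5 is a misprint of 0.05.

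**2. The plan's own figure, TB1 version.** A one-sample formula gives [11.7 × (1.960 + 1.282)/9]² = 17.8, so 18. A two-group comparison needs twice that, 35.5, so 36 (37 with the t-test). The two versions share the number 18 but do not size the same test.

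**3. Family-wise error by reading.** I simulated trials of five arms with 18 per arm under no difference between arms, with two-sample t-tests (at least 100,000 trials, standard error at most about 0.14 percentage points). In brackets is the Bonferroni bound, the number of tests × 0.017.

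| Family | Tests | At 0.017 | At unadjusted 0.05 |
|---|---|---|---|
| Three products against normal eggs | 3 | 4.5% (5.1%) | 12.5% |
| Four arms against one control | 4 | 5.8% (6.8%) | 15.5% |
| Three products against either control, plus control against control | 7 | 9.2% (11.9%) | 23% |

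At exactly 0.05/3 the first family gives 4.4%.

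**4. Power of the family that Section 2 supports.** Three contrasts at 0.0167 with 18 per arm have power 0.90 each at SD 7%. At SD 11.7% the power is 0.43, and 48 per group would be needed for 90%.

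**The case against.** Much can be said for the protocol. Section 2 does state the primary comparison, and with three modified products it yields exactly three contrasts. At 0.017 these hold the family-wise error below 5%. The misprinted 0.5 could never be applied. TB1 is a margin comment in the past tense that shortens the Dutch text, and its silence on Bonferroni is not an instruction to test unadjusted. Contrasts within the repeated-measures model are commonly left to a statistical analysis plan, which may exist.

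Most of this stands, and it limits the conclusion. A reader might infer that the primary comparisons are not error-controlled. The documents do not support that, because one reasonable reading controls the error. A reader might also count three rival levels, but there are two: a corrected 0.017 and an uncorrected 0.05. Nor should the worst case be quoted as the size of the problem. Testing all ten pairs would give 11.9% at 0.017 and 28.5% at 0.05, but no section plans all ten pairs.

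What does not stand is the appeal to an analysis plan. The mismatch of three with five groups, the two meanings of control, and the two levels are contradictions inside the protocol, and its sample size rests on them. The favourable reading also has to be built from Section 2. Section 4.4 speaks of three groups, not of three contrasts among four.

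**Conclusion.** The point holds as an internal inconsistency in what defines the primary claim. The protocol does not fix which contrasts are primary, against which arm, or at what level. Whether the error is controlled therefore cannot be read from it. The family-wise error is about 4.5% to 9% at 0.017 and about 12% to 23% at an unadjusted 0.05, depending on which sentences are followed.

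These figures assume 18 completers per arm, equal variances and pairwise t-tests. Section 8 plans a repeated-measures model, so they indicate the scale and are not the exact error of the final analysis.

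Two further inferences would go too far. The first is that the repair is wording alone: it leaves 18 per group adequate only if the Dutch SD of 7% is the operative one. The second is that comparison with normal eggs always isolates enrichment. It does not for the lutein product, which Section 5.6 describes as a buttermilk drink containing one yolk. That contrast also reflects the vehicle.

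**What to change.** 1. In Section 4.4, correct 0.5 to an overall two-sided alpha of 0.05.
2. Replace the reference to three groups by three named primary contrasts in line with Section 2: lutein egg, zeaxanthin egg and lutein-egg product, each against the normal-egg arm. Test each at 0.05/3 = 0.0167, or use Holm.
3. Give the no-egg arm its own name, for example the no-intervention arm. Make its comparisons secondary, and correct both sentences on the control group in the Summary.
4. Align the Dutch text and TB1 on one alpha, one device and one SD. State that 18 per group gives 90% power at 0.0167 only with an SD of 7%.
5. Note that the contrast for the buttermilk product combines enrichment with a difference in vehicle.

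**Cost.** Comparisons with the no-egg arm lose primary status. At SD 7% the sample size is unchanged. If 11.7% is adopted, the sample size must be reconsidered (48 per group before dropout). If the sponsor prefers four primary contrasts against one control, the level is 0.05/4 = 0.0125. At SD 7% that needs 19 per group, 22 after 10% dropout, or 110 in total.

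### Section 4.4 uses the 9% rise expected on the lutein egg as the between-group difference, so the stated 90% power holds only against a comparator that does not respond, and the primary objective's comparator is a normal egg

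*Protocol*

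**What the plan says.** Section 4.4 starts from supplement studies (5% more macular pigment per month on 10 mg lutein, and a similar rise on 20 mg). It argues that lutein is more available from egg, and so expects 3% per month on an egg holding at most 1 mg: "We therefore anticipated a 3% monthly increase in MPOD, resulting in a 9% MPOD increase over the study period". This is a rise over time in subjects who eat the egg.

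The next Dutch paragraph turns it into a difference. It announces a comparison of three groups, "We willen drie groepen met elkaar vergelijken", without naming them, and concludes: "Om een significant verschil in macula pigment dichtheid van 9% aan te kunnen tonen zijn dan 18 proefpersonen per groep". The other inputs there are a reflectometer error, "die een meetfout heeft van 7" per cent, an adjusted alpha, "Bonferroni correctie 0.017", and beta 0.1. No expected change in any comparator is given.

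Section 2 sets the primary objective as "the changes after consumption of modified eggs compared to normal eggs". The Summary says "The trial group will receive the modified eggs or egg product while the control group will receive conventional egg", although its study design paragraph also lists a no-egg group. The composition table (Summary, 4.5 and section 5) gives the normal egg 0.16778 mg lutein and 0.08504 mg zeaxanthin, and the lutein egg 0.921422 mg and 0.137318 mg.

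**The concern.** A rise from baseline equals a between-group difference only when the other group stays where it started. That is a natural planning assumption for subjects who eat no extra eggs. It is hard to square with a daily normal egg, which supplies some of both carotenoids in the same yolk. The protocol's argument for expecting 3% per month from under 1 mg, namely better availability from egg, applies to the normal egg as well.

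At stake is the power of the comparison named in the primary objective. If the normal egg produces any rise, the net difference is below 9% and beta exceeds 0.1, even with every other input of 4.4 accepted. A null result for modified against normal eggs would then carry less weight than the stated power suggests.

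**Working it through.** **Inputs.** Difference 9%, SD 7%, beta 0.1 and 18 evaluable per group come from the Dutch text of 4.4. Alpha is taken as 0.05/3 = 0.0167: the printed 0.5 must be 0.05, since only that gives the Bonferroni value 0.017. Two-sided testing is assumed because sidedness is not stated.

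**Reproducing the plan.** For a two-sample t-test with n per group, the noncentrality is δ / (SD × √(2/n)). At n = 18 the denominator is 7 × √(2/18) = 2.333, and the critical value on 34 df is 2.518. With δ = 9 the noncentrality is 9/2.333 = 3.857 and power is 90.3%. Solving for 90% gives n = 17.9, so 18; then 18/0.9 = 20 with dropout. The plan's figure is reproduced as a two-group comparison with a 9% difference between groups.

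**Carotenoid content of the normal egg relative to the lutein egg.**
- Lutein: 0.16778/0.921422 = 18.2%.
- Lutein plus zeaxanthin: 0.25282/1.05874 = 23.9%.

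**Allowing for a normal-egg response.** Let s be the normal-egg rise as a share of the lutein-egg rise. Then δ = 9 × (1 − s), with SD, alpha and n as above. The value of s is an assumption in every row; the protocol gives none.

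| s | Normal-egg rise | Net difference | Power at 18 per group | n per group for 90% |
|---|---|---|---|---|
| 0 | 0% | 9.00% | 90% | 18 |
| 5% | 0.45% | 8.55% | 87% | 20 |
| 10% | 0.90% | 8.10% | 82% | 22 |
| 18.2% (lutein ratio) | 1.64% | 7.36% | 73% | 26 |
| 23.9% (lutein + zeaxanthin ratio) | 2.15% | 6.85% | 66% | 30 |
| 30% | 2.70% | 6.30% | 58% | 35 |
| 50% | 4.50% | 4.50% | 29% | 67 |

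**What would preserve 90%.** Under proportionality to lutein, a net 9% needs a lutein-egg rise of 9/(1 − 0.182) = 11.0% over the study.

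**The case against.** **The comparator.** Section 4.4 does not say which three of the five groups it compares. A no-egg arm exists, and the Summary's study design paragraph calls a group that eats no additional eggs the control. Against that arm, using 9% as the difference is defensible. This stands, and it limits the point: the calculation may suit one comparison in the trial, but not the one that section 2 makes primary.

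**The effect may be conservative.** The Dutch text presents 3% per 4 weeks as a minimum; the English comment drops this. Taken literally over 90 days, it gives 3 × 90/28 = 9.6%. Under proportionality the net is then 7.9% and power about 80%. A true rise of about 11% would absorb the whole loss. This also stands in part, but the calculation uses 9%, and the protocol nowhere claims 11%.

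**Proportionality.** A reader might infer that power simply is 73% or lower. The documents do not support that. They give no dose-response for eggs, and a less-than-proportional normal-egg response leaves power at 82% to 87% in the rows above. The similar rise reported at 10 and 20 mg hints at a flattening curve, which would push power below 73%, but those are supplement doses far above any egg in this trial.

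**The English comment.** A reader might also carry the subtraction over to its inputs ("The repeatability of the QuantifEYE is 11.7" per cent, alpha 0.05). These give 18 only by a one-sample normal formula. A one-sample test of change has no comparator, so there is nothing to subtract and this point does not arise there. If those inputs are put into a two-group t-test at 18 per group, power is 61% for 9% and 45% for 7.36%. That the comment's inputs do not support 18 per group for two groups is a separate matter.

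**Conclusion.** The point holds in a limited form. Section 4.4 takes a rise from baseline as a between-group difference, and its beta of 0.1 is reproduced only with a zero response in the comparator. For modified against normal eggs the stated 90% is therefore not supported. How far power falls depends on a normal-egg response that the protocol does not give: from 87% at a 5% share to 29% at a 50% share, with 73% if the response is proportional to lutein.

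These figures accept the plan's own SD of 7%, two-sided alpha of 0.05/3 and 18 evaluable per group. They also treat 9% as the lutein-egg rise rather than as a floor. They show what the omitted subtraction does to the plan's own calculation, and are not a forecast of the trial's actual power.

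**What to change.** In section 4.4:

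1. State that 9% is the expected change from baseline on the lutein egg, and that beta = 0.1 at 18 per group holds only against a comparator that does not respond.
2. Name the groups that the calculation compares.
3. State an expected normal-egg response, labelled as an assumption and shown with a range.
4. Restate the power for modified against normal eggs on the net difference; for example, about 73% at 18 evaluable per group if the response is proportional to lutein, on the plan's own SD and alpha.

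This changes the wording of one section. Enrolment and the study products stay as they are. The cost is that the protocol must report a less favourable power for its primary comparison.

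### Section 4.4 reaches 18 per group from two incompatible sets of inputs, and neither, as stated, supports 90% power for the between-group comparison of change

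*Protocol*

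**What the plan says.** Section 4.4 of the Protocol holds two accounts of the same sample size.

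- **Dutch text.** The instrument is the Macular Pigment Reflectometer, "die een meetfout heeft van 7" per cent. Three groups are to be compared with each other ("We willen drie groepen met elkaar vergelijken"). The conclusion is "Om een significant verschil in macula pigment dichtheid van 9% aan te kunnen tonen zijn dan 18 proefpersonen per groep", with beta 0.1 and alpha corrected to 0.017. The uncorrected alpha is printed as 0.5, evidently a slip for 0.05, since 0.05/3 = 0.0167.
- **English comment beside it (TB1).** "The repeatability of the QuantifEYE is 11.7" per cent. The effect is worded as a rise, "resulting in a 9% MPOD increase over the study period". Alpha is 0.05 with no correction, beta is 0.1, and "this yielded 18 subjects per group [59".

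Both add 10% dropout to reach 20 per group. Section 2 sets the primary objective as the change in macular pigment after modified eggs compared with normal eggs. Section 8 plans a repeated-measures model with time as within-subject factor. No SD of change and no between-subject SD appears anywhere in the Protocol.

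**The concern.** The device, the error figure and the alpha all differ between the two accounts, yet the answer is the same. That suggests that the two calculations are not of the same kind. The quantity a between-group comparison of change needs is the between-subject SD of change. Section 4.4 gives two instrument figures in its place: a measurement error, and a repeatability that it does not define.

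The 9% also needs care. It is derived as the expected rise over three months under about 1 mg of egg lutein a day, then used as the difference between groups. That assumes, without saying so, no rise with normal eggs.

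At stake is the stated power. If 90% is not what the design delivers, a non-significant comparison could be given more weight as evidence against an effect than it can bear.

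**Working it through.** **Inputs from Section 4.4:** difference 9%; beta 0.1 (z = 1.2816); 7% with alpha 0.05/3 = 0.0167 (printed as 0.017); 11.7% with alpha 0.05. Sidedness is not stated, so two-sided is assumed.

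**Formulas (normal approximation), with z the sum of the alpha and beta quantiles:**
- one-sample or paired: n = z² × (SD/9)²
- two-sample, per group: n = 2 × z² × (SD/9)²

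Power and final n below use the noncentral t distribution.

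**1. Reproducing 18 from the English inputs.** z = 1.960 + 1.282 = 3.242, and (11.7/9)² = 1.69.
- One-sample or paired: 3.242² × 1.69 = 17.8, so 18. The t-based answer is 20, and power at 18 is 86.7%.
- Two-sample: 2 × 17.76 = 35.5, or 37 per group with the t distribution. Power at 18 per group is 61%.
- A one-sided test does not rescue it: the two-sample n is then 29 to 30.

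With 11.7% as the SD, 18 is therefore the within-group number by normal approximation.

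**2. Reproducing 18 from the Dutch inputs.** z = 3.676. Two-sample: 2 × 3.676² × (7/9)² = 16.3, or 18 per group with the t distribution. Power at 18 is 90.3%. The arithmetic is right, provided 7% is the SD of the analysed change.

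**3. If 7% is the error of one reading.** A change is the difference of two readings, so error alone gives an SD of 7 × √2 = 9.9%. The two-sample n is then 35 per group and power at 18 is 59% at alpha 0.0167 (75% at 0.05).

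**4. Other readings of the 11.7%.**
- 1.96 × the within-subject SD: 11.7/1.96 = 5.97, and the SD of change is 5.97 × √2 = 8.4%.
- 95% coefficient for the difference of two readings: the SD of change is 11.7/1.96 = 6.0%.
- SD of one reading: the SD of change is 11.7 × √2 = 16.5%.

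**5. Two-sample results for a 9% difference, 18 per group:**

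| SD of change | Basis | Power, alpha 0.05 | Power, alpha 0.0167 |
|---|---|---|---|
| 6.0% | 11.7% as 95% coefficient for differences | 99% | 97% |
| 7.0% | 7% as the whole SD of change | 96% | 90.3% |
| 8.4% | 11.7% as 1.96 × within-subject SD | 87% | 75% |
| 9.9% | 7% as error of one reading | 75% | 59% |
| 11.7% | 11.7% as SD of change | 61% | 43% |
| 16.5% | 11.7% as SD of one reading | 35% | 20% |

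Where the SD of change is built from measurement error alone, true variation in response between people would raise it and lower the power. The 43% combines the English SD with the Dutch alpha; neither account states that pair.

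**6. Limits.** Eighteen per group gives 90% power only if the SD of change is at most 8.1% (alpha 0.05) or about 7.0% (alpha 0.0167). The difference detectable with 90% power is 12.7% (SD 9.9, alpha 0.0167), 13.0% (SD 11.7, alpha 0.05) or 15.0% (SD 11.7, alpha 0.0167).

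**7. Dropout.** 18/0.9 = 20, which is correct. If all 20 completed, power would be about 65% (SD 9.9, alpha 0.0167) or 66% (SD 11.7, alpha 0.05).

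**The case against.** The strongest defence is that the Dutch calculation is a proper between-group one and is arithmetically correct. The objection to it is to the choice of SD, and depends on reading the measurement error as that of a single reading. Section 4.4 does not define it. If 7% were the SD of change, 18 would stand. This is right, and a reader should not infer an arithmetic slip in the Dutch text. But the Protocol calls the figure an instrument's error and never says that it covers variation in change between people.

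A second defence is that the 11.7% stands in a margin comment written in the past tense, and that repeatability has several meanings. On one, power at 18 is 87% at alpha 0.05, close to plan. On another it is 99%, and 18 suffices on measurement error alone. So a reader might infer that the English inputs prove an underpowered trial, and the Protocol does not support that. It is equally silent in favour of the lenient readings, which leave out variation in response.

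Two further inferences go too far:

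- Because normal eggs hold 0.168 mg lutein against 0.921 mg in the lutein egg, a reader might shrink the 9% in proportion. Section 4.4's own premises do not support a proportional response: it says 10 mg and 20 mg of supplement give a similar rise, and expects 3% per four weeks from at most 1 mg in egg against 5% a month from 10 mg.
- Because the zeaxanthin egg's lutein (0.174 mg) is almost that of the normal egg, a reader might conclude that 9% cannot apply to it. The endpoint is total macular pigment, which the Summary ties to both carotenoids, and that egg holds 0.487 mg zeaxanthin against 0.085 mg. The 9% is not separately justified for that arm, which is a weaker statement.

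**Conclusion.** Wrong as written. Section 4.4 presents 90% power for a 9% difference on two bases that cannot be reconciled, and as described neither establishes that power for the comparison in the primary objective. If 11.7% is the SD, 18 answers a one-sample or paired question, and power for two groups is 61% at alpha 0.05. If 7% is the error of one reading, power is 59% at the corrected alpha, before any variation in response.

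These figures assume two-sided tests, 18 evaluable subjects per group and a true difference of 9%. They are conditional on what the two error figures mean. The finding is that the stated 90% is unsupported; the Protocol does not fix the true power, which could be adequate if the SD of change is about 7% or less (8.1% at alpha 0.05).

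**What to change.** Replace Section 4.4 with a single two-sample calculation on change in macular pigment optical density, enriched egg versus normal egg. It should:

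- name one instrument and say what its error figure is (error of one reading, repeatability coefficient, or SD of change);
- state the SD of change used, its source, and whether it includes variation in response;
- state the test, its sidedness and the alpha actually used, and correct the printed 0.5;
- say that 9% is the expected rise under the lutein-enriched egg, used as a between-group difference by assuming no rise with normal eggs, and that it is not separately justified for the zeaxanthin arm.

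Keep 20 per group. Replace the 90% claim with the power, or the difference detectable at 90%, under the stated SD and alpha. On the inputs examined here that difference is 12.7% to 15.0%, each figure to be given with its SD and alpha.

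The cost is rewriting one section. No subjects, visits or analyses are added. The stated power becomes less favourable unless a documented SD of change supports it.
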